## Abstract

**Background:**

Preexposure prophylaxis (PrEP) is a key biomedical HIV prevention strategy that relies heavily on adherence for optimal effectiveness. In China, most PrEP users purchase their medication online, making it challenging to monitor and support adherence effectively.

**Objective:**

This protocol aims to describe a digital intervention developed to monitor and improve the medication adherence of real-world e-consumers of PrEP and an evaluation plan assessing its acceptability, feasibility, and effectiveness.

**Methods:**

The Real-Time Monitoring and Precision Intervention for HIV PrEP Adherence (REMOTE) trial is a parallel-group, open-label, online-delivered, active-controlled, and stratified randomized controlled trial conducted among 430 e-consumers of PrEP (320 event-driven regimen users and 110 daily regimen users) in China. People who have purchased PrEP online, have taken PrEP in the previous 3 months, and plan to continue for the next 6 months will be stratified by regimen type and randomized into control and intervention groups at a 1:1 ratio. A WeChat-based digital platform will deliver the REMOTE intervention. The monitoring module follows ecological momentary assessment principles. The intervention design is guided by the stages of change theory, tailoring strategies to different nonadherence risks based on monitoring results. Intervention components include low-risk (health education and an artificial intelligence chatbot), medium-risk (peer forum and admonitory education), and high-risk (customized reminders and physician counseling) strategies. The control group will use a simplified platform with only real-time monitoring. The primary outcome is the proportion of participants achieving optimal adherence for 6 months, assessed via real-time monitoring and validated via surveys at baseline and the 1-, 3-, and 6-month follow-ups. Secondary outcomes include PrEP adherence knowledge, self-efficacy, risk perception, adherence barriers, stigma, and social support, measured via surveys. Intention-to-treat analysis will be conducted.

**Results:**

Funding for the study was approved in March 2024. Ethics approval for the study was granted in July 2024. The pilot trial was completed in November 2025. Baseline data collection commenced in January 2026. By February 5, 2026, recruitment and baseline data collection were completed, with 448 participants enrolled. The data have not been viewed by the research team. The intervention is currently ongoing, and the study is expected to conclude in August 2026. Results are anticipated to be published in early 2027.

**Conclusions:**

The REMOTE trial pioneers a real-time monitoring and precision intervention for e-consumers of PrEP. Leveraging technology and ecological momentary assessment, it delivers a personalized, real-time intervention that is crucial for adherence. The findings could significantly impact future HIV prevention strategies.

**Trial Registration:**

Chinese Clinical Trial Registry ChiCTR2400088278; https://www.chictr.org.cn/showproj.html?proj=236414

**International Registered Report Identifier (IRRID):**

DERR1-10.2196/92750

## Introduction

HIV and AIDS continue to be a severe public health threat worldwide [1]. Preexposure prophylaxis (PrEP) is a highly effective biomedical strategy for preventing HIV infection, and it is strongly recommended for individuals at higher risk of HIV acquisition by the World Health Organization [2]. PrEP can reduce the risk of HIV transmission significantly across all populations when taken as instructed [3]. However, the effectiveness of PrEP heavily depends on optimal medication adherence. Previous studies have shown that, for every 10% reduction in PrEP adherence, the effectiveness of PrEP is reduced by 13% [4,5]. Oral PrEP offers 2 medication regimens currently: daily PrEP and event-driven PrEP [6]. For daily PrEP, users must take 1 pill every 24 hours, starting at least 7 days before engaging in high-risk behavior [7]. For event-driven PrEP, known as the “2-1-1” protocol, users are required to take 2 pills 2 to 24 hours before anticipated sexual activity, followed by 1 pill 24 hours after the initial dose and another pill 48 hours after [8]. A large body of literature shows that suboptimal PrEP adherence is common worldwide, with the reported prevalence of good adherence ranging from 38% to 97%, where the proportion of good adherence among daily users is significantly higher than that among event-driven users [9-12].

In China, PrEP was officially approved by the government in 2020 [13], and most users are young men who have sex with men of Han ethnicity, with approximately 70% obtaining their medication through online platforms in real-world settings [14-16]. On these platforms, people who are willing to purchase PrEP are first required to complete an online screening questionnaire for PrEP eligibility (eg, recent HIV testing results and contraindications to PrEP). A physician then reviews the screening questions remotely and issues an electronic prescription if the clients meet PrEP eligibility. In China, obtaining PrEP through traditional clinical channels requires visiting designated hospitals, undergoing rapid HIV testing, and receiving a physician’s risk assessment, which can be time-consuming. In contrast, online purchasing platforms allow users to complete the screening questionnaire to obtain PrEP remotely, offering a more convenient and accessible alternative. Moreover, compared to traditional channels, e-commerce platforms such as HeHealth, the biggest and most popular internet hospital for selling PrEP in China, occasionally offer promotional discounts, making online access slightly more affordable. Despite the advantages, there are unique challenges for e-consumers of PrEP to achieve optimal medication adherence compared to traditional clinic clients due to the nature of online sales, such as lack of face-to-face communication with physicians and frequent follow-up and counseling regarding their adherence and HIV risk.

Our recent cohort study using surveys showed that the prevalence of optimal adherence (ie, strictly following the 2-1-1 guidelines for event-driven users and taking 1 pill per day for daily users) among 657 e-consumers of PrEP in China ranged from 80.7% to 87.8% for the daily regimen and 38.6% to 44.1% for the event-driven regimen (the main medication regimen chosen by real-world Chinese users). The main factors associated with nonadherence included sociodemographics (eg, younger age), behavioral factors (eg, chemsex and multiple sex partners), and psychosocial factors (eg, forgetfulness, low self-efficacy, and PrEP stigma) [17]. Previous studies have also identified barriers to PrEP uptake and adherence, such as cost, access, and stigma associated with PrEP [11]. Therefore, there is an urgent need to develop interventions to improve medication adherence for real-world PrEP users. Previous intervention research has used electronic pill boxes, mobile phone apps (visually confirming taking the medication), and ingestible sensors to monitor PrEP adherence in a timely manner and developed digital interventions (eg, message reminders and remote counseling) to improve adherence, but their target groups were all offline clinic PrEP users and were mostly daily regimen users [18-20]. As mentioned above, e-consumers and event-driven regimen users account for most real-world PrEP clients in China, and they face unique challenges with respect to medication adherence that need special attention.

To address these gaps, this study aims to develop a digital platform to achieve real-time monitoring of PrEP adherence based on the principles of ecological momentary assessment (EMA); deliver a just-in-time adaptive intervention guided by the stages of change theory (SCT) and transtheoretical model (TTM); and conduct a randomized controlled trial to evaluate the effectiveness, acceptability, and feasibility of the digital intervention. EMA is a sampling approach that gathers repeated, real-time data on participants’ experiences and behaviors in their natural environments and has become increasingly used in health behavior monitoring with the proliferation of smartphones and internet access [21-24]. The SCT posits that behavior change is a continuous process of 5 distinct stages: precontemplation, contemplation, preparation, action, and maintenance; different intervention strategies should be applied for people at different stages [25]. Moreover, by identifying a participant’s stage, the intervention can deliver tailored, stage-specific strategies that build self-efficacy and support sustained adherence. Different stages receive different interventions, forming a continuous process aligned with the user’s risk level and incorporating the 10 processes of change from the SCT. This framework also acknowledges relapse as part of behavior change, allowing for timely, real-time support to re-engage users. By addressing the specific needs of e-consumers, this study not only fills a critical research gap in the Chinese context but also offers valuable insights and practical implications for promoting medication adherence in similar settings across other low- and middle-income countries.

## Methods

### Study Design

The Real-Time Monitoring and Precision Intervention for HIV PrEP Adherence (REMOTE) trial is a parallel-group, open-label, active-controlled, stratified randomized trial being conducted from November 2025 to August 2026. Eligible e-consumers of PrEP have been enrolled, stratified by regimen, and randomized into the intervention and control group at a 1:1 ratio. The intervention group will be asked to use the full version of a WeChat-based digital platform with real-time monitoring and precision intervention functions developed by the research team for 6 months. The control group will access a simplified version of the platform containing only the real-time monitoring function designed for adherence data collection to minimize recall bias for both groups. As the monitoring system may also improve PrEP adherence, it is considered as an active control strategy. All the participants will be asked to complete the baseline and 1-, 3-, and 6-month surveys. This study protocol was developed in accordance with the SPIRIT (Standard Protocol Items: Recommendations for Interventional Trials) checklist.

### Population

People who (1) are aged 18 years and older, (2) have purchased PrEP through HeHealth (the largest internet hospital selling PrEP in China, formerly known as BluedHealth) and passed the required risk assessment and health examination confirming their eligibility for PrEP use at the time of purchase, (3) have taken PrEP in the previous 3 months and have plans to continue taking the medication in the following 6 months, and (4) provide oral informed consent will be included in the study. People who are (1) incapable of communicating and reading and (2) unable to use mobile phones and the WeChat app will be excluded from the study. This exclusion criterion was established to ensure that all participants can comprehend the study materials and effectively engage with the digital platform throughout the study.

To recruit participants, HeHealth staff will distribute recruitment messages containing a QR code linking to the research team’s WeChat account to potentially eligible individuals via the platform’s internal messaging system. Interested individuals may scan the QR code to contact the research team through WeChat, after which eligibility screening based on the inclusion criteria will be conducted by the research staff. All recruitment materials and procedures used by the research team will ensure neutrality, ethical compliance, and the absence of sales incentives. Information on the purpose of the study, specific study procedures, possible risks and discomforts, potential benefits, contact, and the rights of participating individuals will be clearly stated by the recruiters and presented in the electronic informed consent form. Electronic informed consent will be obtained before any data collection. Once recruited into the study, participants will be assigned a unique ID number for logging into the digital platform and responding to the baseline and follow-up electronic questionnaires.

### Sample Size Planning

The sample size was calculated based on the adherence data we obtained from the previous cohort study and the available financial and human resources [17]. Among event-driven users, a sample size of 320 can detect at least a 17.5% difference in the proportion of optimal adherence between the 2 groups assuming that the proportion of optimal adherence in the control group is 45% (estimated proportion of optimal adherence in the control group, *p*_2_=0.45), the rate of loss to follow-up is 20% (not completing the electronic questionnaire sent during follow-up visits), the level of significance is α=.05 (*Z*_α_=1.64), and the statistical power is β=.8 (*Z*_β_=0.84). Among PrEP daily users, a sample size of 110 could detect at least a 17.5% between-group difference assuming a 60% proportion of optimal adherence in the control group (*p*_2_=0.60), a 10% loss to follow-up rate, a significance level of α=.05 (*Z*_α_=1.64), and a statistical power of β=.8 (*Z*_β_=0.84). Therefore, a minimum of 430 participants will be enrolled in this study.

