### Outcomes

The primary outcome of this study is optimal PrEP adherence over the 6-month study period, defined as a binary outcome (optimal vs suboptimal adherence) and assessed separately for event-driven and daily PrEP users. Adherence will be measured primarily using EMA data collected through the PLP Camp platform version 2.0, whereas survey data collected at baseline and follow-up visits will be used to support interpretation and cross-validation of adherence-related measures.

For daily PrEP users, each PLP Camp check-in will record whether the participant has taken 1 PrEP pill within the preceding 24 hours. Adherence will be calculated as the proportion of days with reported pill intake out of all days under observation during each monitoring period. In constructing this outcome, days without a submitted PLP Camp check-in will be operationally treated as days without reported pill intake. Daily users with adherence of 80% or higher during the relevant monitoring period will be classified as having optimal adherence, whereas those with adherence below 80% will be classified as having suboptimal adherence [4,8,35].

For event-driven PrEP users, each PLP Camp check-in will capture sexual behavior and PrEP use occurring within the reporting interval, defined as the time since the previous check-in up to a maximum of 72 hours. Adherence will be assessed at the level of reported sexual encounters according to the standard 2-1-1 regimen. A reported sexual encounter will be classified as adherent if the participant reports taking 2 PrEP pills 2 to 24 hours before sex, 1 pill 24 hours after the initial dose, and 1 additional pill 48 hours after the initial dose. Event-driven users will be classified as having optimal adherence if all reported sexual encounters during the relevant monitoring period meet these dosing requirements; otherwise, they will be classified as having suboptimal adherence. Intervals without a submitted PLP Camp check-in will be treated as intervals without a reported sexual encounter, and therefore, event-level adherence will be assessed only for reported sexual encounters.

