### Statistical Analysis

All analyses will follow the intention-to-treat principle, whereby all randomized participants will be analyzed according to their assigned study group regardless of intervention uptake, regimen changes, or follow-up completeness. Baseline characteristics will be summarized by study group using appropriate descriptive statistics.

The primary analysis will assess between-group differences in optimal PrEP adherence over time. As the primary outcome is binary and repeatedly measured, generalized linear mixed-effects logistic regression models will be used, including fixed effects for study group, time, and the group-by-time interaction and a participant-level random intercept to account for within-participant correlation. Prespecified baseline covariates will be included to improve precision and adjust for residual imbalance. Effect estimates will be presented as odds ratios with 95% CIs.

Adherence outcomes will be constructed according to the prespecified regimen-specific definitions described above. For daily PrEP users, days without a recorded PLP Camp check-in during each monitoring period will be operationally treated as days without reported pill intake based on previous literature [36,37]. For event-driven PrEP users, adherence will be assessed only for reported sexual encounters according to the standard 2-1-1 regimen; intervals without a submitted PLP Camp check-in will be treated as intervals without a reported sexual encounter.

Secondary outcomes will be analyzed using mixed-effects models appropriate to outcome type, with fixed effects for study group, time, and the group-by-time interaction and participant-level random effects. All tests will be 2 sided, with statistical significance defined as *P*<.05. Analyses will be conducted using the R software.

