### Strengths and Limitations

While this study offers a promising and innovative approach, several limitations should be acknowledged. First, participants will be conveniently recruited from PrEP clients of a single internet hospital, HeHealth, in China. Although HeHealth is currently the largest online platform for obtaining PrEP in China, the use of a single-platform sample may limit the generalizability of the findings to broader populations of PrEP users. Second, both PrEP adherence monitoring data and survey data will rely on self-report, which may be subject to social desirability bias and recall bias and, therefore, may lead to overestimation of adherence. Third, loss to follow-up may pose a challenge because of the online recruitment strategy and the relatively long follow-up period. Although a 10% to 20% attrition rate has been considered in the sample size calculation, higher-than-expected dropout could still reduce the statistical power of the study. Fourth, the effectiveness of the intervention may vary according to the level of participant engagement with the platform. Because the intervention depends on users actively interacting with its functions, such as behavior recording, health education materials, medication reminders, expert consultation, and the chatbot, low engagement may weaken its effect on adherence and warrants further investigation into factors that promote or hinder sustained use. In addition, as behavioral monitoring itself may influence medication adherence through self-awareness or self-tracking effects, this trial can only estimate the incremental effect of the precision intervention functions beyond the monitoring function rather than the effect of the full digital platform compared with usual care. Finally, this study is limited to oral PrEP and does not include all PrEP dosage forms. With the introduction of long-acting injectable PrEP, adherence challenges may differ across modalities. However, oral PrEP is expected to remain the predominant form of PrEP use in China for the foreseeable future, and therefore, this study is focused specifically on oral PrEP users.

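### The sample size removes losses defined by the questionnaire, but the primary outcome comes from platform check-ins and keeps silent daily users in the comparison, so the stated 80% power does not describe the planned analysis

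*Protocol article*

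**What the plan says.** In the protocol article, Sample Size Planning states for event-driven users that "a sample size of 320 can detect at least a 17.5% difference in the proportion of optimal adherence between the 2 groups", with a control proportion of 45% and 80% power. The loss assumption there is 20%, defined as "not completing the electronic questionnaire sent during follow-up visits". For daily users it gives 110 participants, a control proportion of 60%, the same 17.5-point difference and 10% loss, without repeating the definition of loss.

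Outcomes names a different source for the primary endpoint: "Adherence will be measured primarily using EMA data collected through the PLP Camp platform version 2.0". Surveys have a supporting role. For daily users, a day with no check-in counts as no pill, and 80% of days is the threshold for optimal adherence. For event-driven users, an interval with no check-in counts as having no reported encounter, and only reported encounters are judged.

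Statistical Analysis keeps all randomized participants in their assigned groups "regardless of intervention uptake, regimen changes, or follow-up completeness" and makes every test two-sided. Missing Data Handling says the check-in rules belong to the outcome definition and are not imputation. Strengths and Limitations says that "a 10% to 20% attrition rate has been considered in the sample size calculation".

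**The concern.** Dividing n by (1 − loss) is right when lost participants leave the analysis and the difference among those who remain is unchanged. That fits an outcome read from the questionnaire. The outcome here is read from the platform. Someone who skips a survey but keeps checking in is not lost to the primary analysis at all. A daily user who stops checking in is not lost either: that person is retained and scored suboptimal. If the same share of both arms is scored the same way whatever the treatment, the observed difference contracts by that share.

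At stake is how the result will be read. A null finding would be set against a 17.5-point detectable difference at 80% power that was worked out for a different handling of non-response.

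**Working it through.** **Inputs.** From Sample Size Planning: event-driven 45% vs 62.5% with 20% loss; daily 60% vs 77.5% with 10% loss. From Randomization and Blinding: 160 and 55 per arm. From Statistical Analysis: two-sided .05. The platform-silent share d is not given. I assume it equals the stated loss, is equal by arm and means complete silence, and I vary it.

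**Formulas.** With p̄ the mean of p1 and p2, S0 = √[2p̄(1−p̄)] and S1 = √[p1(1−p1)+p2(1−p2)]:
- n per arm = (zα·S0 + zβ·S1)² / (p1−p2)²
- power = Φ{[(p1−p2)√n − zα·S0] / S1}
- arm rate with silent users retained = (1−d)p + d·k, where k = 0 if they are scored suboptimal and 1 if optimal. In both cases the difference becomes (1−d)(p1−p2).

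**Reproducing the plan, event-driven.** S0 = 0.7051 and S1 = 0.6942. With z = 1.96, n = 126.2, so 127 per arm. Then 127/0.80 gives 159 per arm, 318 in total, which matches 320. The printed Z of 1.64 gives 100 per arm and 250 in total, which does not. So 320 is the two-sided design in which 20% leave. With 160 × 0.80 = 128 per arm, power = Φ(0.861) = 80.5%.

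**Reproducing the plan, daily.** Two-sided: 109 per arm, 244 in total after 10% loss. One-sided: 86 per arm, 192 in total. Neither is near 110.

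**Event-driven with silent users retained** (160 per arm, 20% silent; difference 0.80 × 17.5 = 14.0 points):
- scored suboptimal, 36% vs 50%: Φ(0.575) = 71.7%
- scored optimal, 56% vs 70%: Φ(0.640) = 73.9%

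| Silent share | Power if silent users are scored (suboptimal–optimal) | Power if not evaluable |
|---|---|---|
| 0% | 88.5% | 88.5% |
| 5% | 84.8–85.3% | 86.8% |
| 10% | 80.8–81.8% | 85.0% |
| 15% | 76.4–78.0% | 82.9% |
| 20% | 71.7–73.9% | 80.5% |
| 30% | 62.0–65.0% | 75.1% |

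Power falls below 80% at about 11% silence (scored suboptimal) or 12.5% (scored optimal). At 20% silence, 80% power needs a difference among reporters of about 18.8 points (scored optimal) to 19.4 points (scored suboptimal).

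**Daily** (S0 = 0.6555, S1 = 0.6437 for 60% vs 77.5%):
- 55 per arm, no loss: Φ(0.020) = 50.8%
- 49.5 per arm, 10% removed: Φ(−0.083) = 46.7%
- 55 per arm, 10% silent and scored suboptimal, 54.0% vs 69.75%: Φ(−0.263) = 39.6%

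With 49.5 per arm, the smallest difference detectable with 80% power is 24.9 points two-sided.

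**The case against.** A reader might infer that the event-driven stratum is simply underpowered. The documents do not support that, for four reasons.

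- No platform-silence rate is given. Non-return of the questionnaire is not platform silence, inactive users are reminded through WeChat, and below about 11–12% silence this stratum keeps 80% power.
- The class of an event-driven user with no reported encounter is not fixed. The text can be read as scoring such a person optimal, because no encounter fails, or as leaving the person unassessed. Missing Data Handling does expect some missing adherence outcomes. If these users are not evaluable, they do leave the comparison and 80.5% stands.
- Silence may be partial or unequal. With 25% silent in control and 15% in intervention, power is 94.1% if silence is scored suboptimal and 41.3% if optimal.
- At the printed Z of 1.64, power at 20% silence would be 81.4–83.1%. This point carries little weight, because the planned tests are two-sided and 320 reproduces only that way.

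A reader might also blame the daily shortfall on the scoring rule. Most of it arises earlier, because 110 does not follow from the printed inputs. The rule moves power only from about 47% to 40%.

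The attrition sentence in Strengths and Limitations is true as written, and that section separately warns of higher dropout and low engagement. Finally, a two-proportion test only approximates the repeated-measures mixed model, and 448 people were enrolled against the 430 used here, with no split by stratum. All of these objections stand as limits on size. None removes the mismatch between the loss that was planned for and the outcome that will be analyzed.

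**Conclusion.** The point holds in conditional form. The loss allowance is tied to an instrument that does not generate the primary outcome, and it assumes an exit from the analysis that the plan rules out for daily users and leaves open for event-driven users.

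- **Event-driven:** 80% power is not assured at the sponsor's own 20% rate. It is about 72–74% if silent users are scored and 80.5% if they are not evaluable.
- **Daily:** 80% is not reached on any reading examined. It is about 40% with 10% silent and scored suboptimal, and 47–51% before that rule acts.

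The scored figures assume complete silence, equal by arm, at the stated loss rates. All figures assume the stated proportions apply to those who report, and a single two-sided comparison per stratum.

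**What to change.** - **Sample Size Planning:** define loss as stopping platform check-ins, and give an assumed silent share with a range.
- **Outcomes:** state whether an event-driven user with no reported encounter in a monitoring period is optimal, suboptimal or not evaluable.
- **Sample Size Planning:** restate two-sided power and detectable difference per stratum under those rules. On the printed rates, event-driven power is about 72–74% at 20% silence if scored and 80.5% if not evaluable; daily power is about 40–47%. Say that these are two-proportion approximations to the mixed model.
- **Strengths and Limitations:** add that attrition at the planned rates can also dilute the difference, as well as reduce numbers.

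The cost is text and a short recalculation. The stated power becomes less favorable, but no extra participants are needed. Recruitment is complete and the article reports that the data have not been viewed, so the restatement can still be made before any results are known.

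The daily figure of 110 needs its own correction. Redefining loss will not repair it.

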### Randomization and Blinding

Randomization sequences were generated prior to study initiation by an independent statistician using the R software (R Foundation for Statistical Computing). Participants were stratified by PrEP dosing regimen (daily vs event driven) based on their self-report. Within each stratum, participants were randomized in a 1:1 ratio to the intervention or control group using variable block randomization with randomly permuted block sizes of 4 and 6. As a result, each group will have 215 participants, with 160 event-driven users and 55 daily users (Figure 1). The study adopted an open-label design because the nature of the intervention makes blinding infeasible.

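### The 110 daily users do not give 80% power for a 17.5-point difference: on the plan's own inputs power is about 61% with the one-sided Z it prints and about 48% with the 2-sided level it will use

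*Protocol article*

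**What the plan says.** For the daily stratum, the Sample Size Planning section of the protocol article says: "Among PrEP daily users, a sample size of 110 could detect at least a 17.5% between-group difference assuming a 60% proportion of optimal adherence". The 60% refers to controls, attrition is put at 10%, and the error rates are given as "a significance level of α=.05 (*Z*_α_=1.64), and a statistical power of β=.8 (*Z*_β_=0.84". For event-driven users it gives 320 participants for the same 17.5-point difference, with a 45% control rate, 20% loss and the same two Z values. The two totals are added to make 430.

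The Randomization and Blinding section splits these totals: "each group will have 215 participants, with 160 event-driven users and 55 daily users". So 110 is the whole daily stratum, not one arm.

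The Statistical Analysis section says: "All tests will be 2 sided, with statistical significance defined as *P*<.05". The Outcomes section has the primary outcome assessed separately in the two regimens.

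**The concern.** Two things do not fit. First, 110 is too small for the effect, control rate and loss given in the same sentence. Second, a Z of 1.64 is the one-sided 5% value, while the analysis section commits to 2-sided tests at 5%.

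The article makes a separate detectable-difference claim for daily users and assesses the primary outcome by regimen, so a reader will expect a daily-only result with 80% power behind it. If the real figure is near one half, a null result in that stratum says little, yet the stated power invites reading it as evidence of no effect. The Strengths and Limitations section mentions loss of power only through dropout above the 10% to 20% allowed for, so it does not warn the reader of this.

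**Working it through.** **Inputs, daily stratum** (Sample Size Planning, unless noted): p2 = 0.60; difference 0.175, so p1 = 0.775; loss 10%; Zβ = 0.84; Zα = 1.64 as printed, or 1.96 for the 2-sided 5% level in Statistical Analysis; 55 per arm (Randomization and Blinding).

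**1. Try to reproduce 110.** Unpooled two-proportion formula:

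n per arm = (Zα + Zβ)² × [p1(1−p1) + p2(1−p2)] / d²

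Variance term: 0.775 × 0.225 + 0.60 × 0.40 = 0.414375; d² = 0.030625.

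- Zα = 1.64: 2.48² × 0.414375 / 0.030625 = 83.2 evaluable per arm; divided by 0.9 this is 92.5, so 93 per arm and **186** in total.
- Zα = 1.96: 2.80² × 0.414375 / 0.030625 = 106.1 evaluable per arm; divided by 0.9 this is 117.9, so 118 per arm and **236** in total.

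Other variants do not rescue the figure. Pooled-variance formulas give about 189 to 192 (1.64) or 242 to 244 (1.96), and the continuity correction gives 216 or 269. Reading 17.5% as a relative change (0.60 to 0.705) needs more than 500. No variant gives 110 in total.

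**2. Power with the planned numbers.** Evaluable per arm: 55 × 0.9 = 49.5. SE = √(0.414375 / 49.5) = 0.0915; z = 0.175 / 0.0915 = 1.913.

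- One-sided: Φ(1.913 − 1.64) = Φ(0.273) = **0.61** (0.60 with pooled variance).
- 2-sided: Φ(1.913 − 1.96) = Φ(−0.047) = **0.48** (0.47 with pooled variance).

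Ignoring loss (55 per arm), power is 64% to 65% one-sided and 51% to 52% 2-sided.

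**3. Difference detectable with 80% power at 49.5 per arm,** control rate 0.60: 22.0 points one-sided and 24.3 points 2-sided (22.3 and 24.9 with pooled variance).

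**4. Cross-check on the event-driven stratum.** p2 = 0.45, p1 = 0.625, 20% loss. Variance term: 0.625 × 0.375 + 0.45 × 0.55 = 0.481875.

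| Zα | Evaluable per arm | Total after 20% loss |
|---|---|---|
| 1.64 | 2.48² × 0.481875 / 0.030625 = 96.8 | 242 |
| 1.96 | 2.80² × 0.481875 / 0.030625 = 123.4 | 310 |

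With pooled variance and 1.96 the total is 315 to 318. The stated 320 therefore matches 1.96, not the printed 1.64. At 160 × 0.8 = 128 per arm, SE = 0.0614, z = 2.852 and 2-sided power is Φ(0.892) = 0.81. That stratum is adequately sized.

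**5. Regimen-stratified overall comparison,** common 17.5-point difference. Variances: 0.414375 / 49.5 = 0.008371 (daily) and 0.481875 / 128 = 0.003765 (event-driven). Inverse-variance SE = 1/√(1/0.008371 + 1/0.003765) = 0.0510; z = 3.434; 2-sided power Φ(3.434 − 1.96) = **0.93**. Detectable difference: 2.80 × 0.0510 ≈ 14 points.

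**6. Effect of over-enrolment.** The article reports 448 enrolled but no regimen split. If exactly 320 were event-driven and all 18 extra participants were daily users, there would be 128 / 2 = 64 per arm, 57.6 after loss. The 2-sided power would be about 54%.

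**The case against.** The strongest reply is that the control rate, not the sample size, is the misprint. The Introduction reports 80.7% to 87.8% optimal adherence among daily users in the cohort on which the calculation is said to rest. With p2 = 0.80, Zα = 1.96 and 10% loss, the formulas give 105 to 114 in total, and power at 49.5 per arm is 80% to 82%. This is a plausible origin for 110. So is using a per-arm figure as a total: before loss, the 2-sided requirement at p2 = 0.60 is 106 to 110 per arm. The article does not settle which happened. It prints 0.60 twice, and on that value the claim fails. What stands is that the sponsor should look up the original calculation before choosing the corrected text.

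Other points have less force.

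- The primary analysis is a covariate-adjusted mixed logistic model on repeated outcomes, so 48% is the power of a single two-proportion comparison, not of that model. This is correct, but the article justifies 110 by the two-proportion calculation and gives no correlation or number of periods from which to work out anything else.
- Loss is defined by uncompleted questionnaires, whereas the outcome comes from platform check-ins, so the 10% reduction may not apply. Dropping it raises 2-sided power only to 51% or 52%.
- Available resources were part of the sizing. A resource limit can explain 110, but it does not make 80% power true.
- With 1.64 the event-driven claim is still true as a minimum (power about 89%). The conflict there is only between the printed Z and the 2-sided tests.
- The bound in step 6 depends on the assumed split, since the number of daily users enrolled is not reported.

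**Conclusion.** The concern holds. On the inputs printed in the article, 110 daily users give about 61% power one-sided or 48% 2-sided, not 80%. The number needed is about 186 or 236. The choice of formula moves power by one or two points and does not change the conclusion. The printed Z of 1.64 contradicts the 2-sided tests in both strata, although the event-driven sample size itself is adequate.

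The result assumes a single comparison of two proportions, a 60% control rate and 10% loss, all taken from the plan. It would change if the intended control rate was near 80%, in which case the article's stated rate is the error. The shortfall concerns the separate daily-user claim. A regimen-stratified overall comparison retains about 93% power, provided the difference is the same in both regimens.

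**What to change.** 1. Check the original calculation and confirm the daily control rate. The rate, the Z value and the 110 must agree with one another.
2. Print Zα = 1.96 in both strata, to match the 2-sided tests.
3. If 0.60 is confirmed, state that 110 daily users with 10% loss give about 48% power for 17.5 points, and that the difference detectable with 80% power is about 24 points. If a different rate was intended, print it with its justification and the resulting power.
4. With 0.60 confirmed, label the daily-only comparison as estimation, reported with its confidence interval, so that a non-significant result is not taken as absence of effect.
5. Add the power of the regimen-stratified overall comparison: about 93% for a common 17.5-point difference, detectable difference about 14 points.
6. Give the enrolled numbers by regimen, so that the power statement can refer to the 448 actually enrolled.

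The cost is wording only, with one stated figure becoming less favourable. Recruitment is closed and the article says the research team has not viewed the data, so the correction can be made now without any suspicion that results influenced it. No extra enrolment is needed.
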